### Interventions

2.5

#### Explanation for the choice of comparators

2.5.1

Throughout the study, all three study groups participate in regular psychosomatic rehabilitation and receive treatment as usual (TAU) in accordance with the guidelines of the German pension insurance for patients with PCS. The control group (group 1) receives only TAU, while the other two groups additionally receive one of the two interventions (group 2 = JOURNAL group; group 3 = FRAME group). Although participants are assigned to groups according to a sequential cohort design, systematic differences or changes in symptom burden should be minimal and attributed to group affiliation and whether a study intervention was received. Which group participants are in depends solely on the timing of their rehabilitation, not on other systematic differences. (see **Figure 1**). Patients are informed about the study on the first day in the rehabilitation hospital. All treating providers are aware of the participants’ condition assignments.

**Figure 1 f1:**
[figure not shown]
The three groups of the study.

#### Intervention description

2.5.2

During psychosomatic rehabilitation, the following points are discussed with all patients as standard and are also important for participation in the study:

Openness to psychotherapeutic interventionsHealthy, active lifestyle, considering the patient’s ability to manage their own strength, reduction of excessive avoidance behaviorAcceptance of illness

The complete manual on the interventions will be published separately. Therefore, the content of the interventions will only be described briefly below.

##### Group 2 – Intervention group “JOURNAL”

2.5.2.1

Patients in group 2 receive TAU and an extra intervention consisting of two short appointments (sessions) lasting no more than 20 minutes. The main point of this intervention is that patients should write down their expectations and imaginations as independently as possible and without assistance from others, e.g. a therapist. Patients in the JOURNAL group are given an accompanying booklet as part of the study, which summarizes the most important information from the individual sessions. The booklet also contains illustrations and worksheets and is the same as in the FRAME group. The booklet is distributed to patients in group 2 on the first days of the rehabilitation by a research assistant who was trained by the team in Ulm. Patients are asked to reflect on their individual expectations of therapy in writing. The individual sessions in which the booklet is discussed include specific reflection questions and exercises designed to help patients process their personal expectations and challenges. In detail, the booklet contains two tasks in which patients are asked to reflect on their expectations, an imagination exercise, and a list of enjoyable activities for after rehabilitation. When leaving the rehabilitation clinic, patients are allowed to take the journal home with them. Only a documentation form completed by the research assistant remains at the clinic.

##### Group 3 – Intervention group “FRAME”

2.5.2.2

Patients in group 3 also receive TAU and a manualized additional intervention consisting of three appointments (see **Table 1**). Patients receive the same booklet as in group 2, but are given therapeutic guidance on how to work through, and develop the content and carry out the imagination exercise together with the therapist. The psychotherapeutic FRAME intervention was developed through an interactive process by a team of interdisciplinary experts (psychologists experienced in inducing placebo effects through expectations, psychotherapists specializing in psychodynamics and cognitive behavioral therapy, hypnotherapists, and medical specialists in psychosomatics, psychiatry, and neurology) and is based on various approaches. The focus of this intervention is primarily on positive expectations (benefit expectations, personal control expectations, side-effect and coping expectations). The structure of the intervention is based on the manual Psy-HEART (38). General therapy principles – such as tangential conversation, avoiding confrontation with resistance and interpretations, selective-authentic responses, integration of psychoeducational elements and working on expanding the individual disease model – were adopted from the psychodynamic manual PISO (39) and are based on the findings of intersubjective systems theory, relational psychoanalysis and attachment theory. Furthermore, hypnotherapeutic elements are integrated, such as an imagination exercise (40). The core element of the intervention is affective-body-oriented work with inner images (imagination exercise).

**Table 1 T1:** Session focus, interventions and duration for each therapeutic session in the FRAME condition.

Session	Session focus and interventions	Duration
1	− Therapeutic relationship − Explanation of the procedure and aim of the intervention, handing out the accompanying booklet − Expectation-focused anamnesis: The current situation and current complaints are discussed briefly. The focus should be *on identifying expectations*. − Focus on benefit expectations: The biopsychosocial disease model should be introduced or taken up (if the patient already knows this) in order to build up the benefit expectations based on this. Expectations regarding the benefits of rehabilitation can be discussed in relation to the current symptoms: *Information about symptom improvement, increase in quality of life and a positive-realistic recovery process through rehabilitation should be addressed.* − *Imagination exercise* (outlook): Considering personal needs, interests, and wishes, the patient should, by the next session, *imagine a picture expressing success and an improved quality of life six months after rehabilitation*. − End of the session: Summarizing what has been achieved and looking ahead to the next two sessions.	50–60 minutes
2	− Beginning o Questions and comments on the patient information (*accompanying booklet*) should be briefly clarified and discussed. By working with a metaphor, control expectations should be increased. − Focus on control expectations (=“control beliefs”) o With reference to part of the first session (○ Personal control expectations) and using a metaphor, the introduction to the imagination exercise is paved. − Increase control expectations with the help of an imagination exercise o The extent to which inner images or imaginations can be used constructively in sports psychology will be illustrated using an example and the fact that this technique is also used in the intervention will be discussed. o In the following, the imagination exercise will be developed using the “VAKOG scheme” (Peter et al., 2015) in a first step (scene from the past). VAKOG stands for seeing (visual), hearing (auditory), feeling (kinesthetic), smelling (olfactory) and tasting (gustatory). o In a second step, the imagination exercise should be carried out and then debriefed. − Conclusion o Summarize what has been worked out and look forward to the last appointment. o The advantages of rehabilitation should be emphasized again at this point. o The imminent end of the intervention should be marked.	20–30 minutes
3	− Greeting with reflection on expectations: The patient should take up their expectations formulated in session I, read them through and reflect on them with the therapist. − Deepening, repetition, practicing of the imagination − Focus on side effect and coping expectations − Pleasant activities: Suggestions for pleasurable activities should be discussed with the patient using a provided list. The patient should select the examples that they consider suitable for themselves to build positive expectations for the future. − Summary and conclusion of the intervention	20–30 minutes

A therapeutic example from the PoCo-FRAME manual is described below. It is based on Laferton et al. (38, p. 24), has been translated into English, adapted to PCS, and supplemented.

Therapist: “I am very pleased that you have agreed to participate in our study. I believe you’ve made a good decision regarding the course of your rehabilitation. The goal of our collaboration is to explore your expectations regarding the success of your rehabilitation. Research has shown that patients who believe in the effectiveness of a treatment often experience better health outcomes afterwards. I´ll help you benefit as much as possible from this effect. I see my role as a confident companion on your journey. There may be times when you have questions or uncertainties — and we’ll address these together. It’s particularly important that we focus on your personal perspective. Please feel free to share your expectations in detail. Today, we’ll primarily focus on what you expect from the rehabilitation process. So, how about you start by telling me about your current situation and your expectations?”

The intervention is carried out as individual therapy in three sessions with one session per week (see **Table 1**). In addition, the patients in the FRAME-group receive a booklet summarizing the most important information from the individual sessions. The booklet also contains illustrations and worksheets that can be completed during or between sessions. Patients should bring the booklet to each session and read the information during the appointments. Therapists receive a documentation form for each patient, which must be completed. After each session, therapists must document which components of the intervention patients have completed.

#### Criteria for discontinuing or modifying allocated interventions

2.5.3

In the event of an acute or significant deterioration of symptoms, including the onset of suicidal tendencies, the intervention will be either modified or discontinued. The decision on this matter rests with the treating therapist or physician at the rehabilitation clinic, who will discuss this with the patient. In such cases, the rehabilitation clinic will initiate appropriate therapeutic treatment. Participants also retain the right to withdraw from the intervention at any time and for any reason, without providing justification. Withdrawal from the study – for whatever reason - has no impact on the rehabilitation measures for patients.

Selection bias cannot be ruled out in studies, especially in real-life studies. The interventions are designed in such a way that we expect a low dropout rate and plan to recruit the calculated sample size. Due to data protection regulations, the data of patients who have dropped out cannot be used for *post-hoc* analysis.

#### Strategies to improve adherence to interventions

2.5.4

As part of the participant information and informed consent process, patients are informed about the importance of consistent and active participation in therapy and intervention sessions. Treatment adherence is assessed using standardized checklists that list the intended content of each session. Therapists document which components of the manual were implemented and which were omitted. In cases where certain elements could not be delivered, the underlying reasons are noted – for example, if the session content was too demanding for the participant due to difficulties with concentration.

#### Relevant concomitant care permitted or prohibited during the trial

2.5.5

All forms of medical treatment and therapeutic interventions are permitted throughout the study and will be systematically documented. All patients will receive TAU during the psychosomatic rehabilitation program. This treatment as usual can vary between rehabilitants, as the patient’s stress limit and symptoms are always considered when planning therapy.

#### Provisions for post-trial care

2.5.6

It is assumed that participants will benefit from the intervention, resulting in an improvement in PCS symptoms. Adverse effects related to study participation are not anticipated.

#### Outcomes

2.5.7

Since the predominant symptoms in patients with PCS vary considerably and the main goal of rehabilitation is to maintain or improve work ability, the Work Ability Index (WAI) is considered the primary endpoint for measuring work ability. The WAI ranges from 7 points (unable to work) to 49 points (full work ability), with higher scores indicating better subjective work ability. Consequently, increases in WAI scores reflect improvements in perceived work ability, whereas lower scores indicate reduced work ability. International studies conducted in recent years in Europe, South America, and Asia show high internal consistency between 0.72 and 0.83. The WAI also correlates highly and significantly with all scales of the Short-Form Health Survey (SF-36) and the General Health Index (r between 0.5 and 0.8) (41). It is therefore a reliable and proven tool in rehabilitation research.

Secondary outcomes include: WHO Disability Assessment Schedule 2.0 (WHO DAS 2.0), PCS symptoms (adapted Regensburg COVID documentation, ReCoRD), somatic symptoms (Patient Health Questionnaire 15, PHQ-15 and Somatic Symptom Disorder B-criteria Scale, SSD-12), depressiveness (Patient Health Questionnaire-9, PHQ-9), anxiety (Generalized Anxiety Disorder Scale, GAD-7), fatigue (Fatigue Scale for Motor and Cognitive Functions, FSMC), post-exertional malaise (DePaul Symptom Questionnaire), expectations regarding rehabilitation and its outcome (Treatment Expectation Questionnaire, TEX-Q), self-efficacy expectations (SWE), and quality of life and general health status (2 items).

In addition, personality questionnaires are used to identify correlations between personality functioning and PCS to provide patients with the best possible psychotherapeutic support in the future. The transdiagnostic personality structure (Operationalisierte Psychodynamische Diagnostik – Strukturfragebogen Kurzform, OPD-SFK) and a scale for perfectionism (Frost Multidimensional Perfectionism Scale – Deutsche Version, FMPS-D) are used for this purpose.

Objective measurements include computer and paper-based tests to assess cognitive performance, such as attention span, memory, and reaction times (Corsi Span Test and Color Stroop Test), 6-minute walk test, blood pressure, and 5-minute pulse measurement at rest to assess heart rate variability. Further measurements include clinical assessments of rehabilitation outcomes and medical evaluation of the ability to work (discharge letter) by the physician. The cognitive assessments are not part of routine clinical evaluations; they are specifically implemented for the purposes of this study.

A comprehensive range of outcomes was selected by a multidisciplinary research team to ensure the future provision of optimal support for patients.

The questionnaires are used in all three groups at the beginning baseline (T1; baseline), at the end of rehabilitation (T2), and six months after rehabilitation program (T3). Rehabilitation usually ends after 3 to 4 weeks. The final measurements for the study are taken during the last psychotherapy session in the final week.

Participants with PCS may experience difficulties using the screen and concentrating. To ensure their comfort and reduce any burden, we have made several adjustments available. Participants have the option to take breaks as needed, complete the questionnaires at their own pace, and even continue at a later time if necessary. Additionally, paper versions of the questionnaires can be provided upon request, and participants can also complete them in their rooms if this is necessary. The assessment sessions are expected to take between 70 and 90 minutes per assessment, depending on the individual condition and needs of the patient.

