#### Participant timeline

2.5.8

A schematic schedule for participants is depicted in **Table 2**.

**Table 2 T2:** Schedule for participants (T1, T2, T3 = time 1, time 2, time 3).

Assessments	T1 on admission to rehabilitation	T2 on discharge from rehabilitation	T3 6 months after rehabilitation
questionnaires	X (online in the clinic)	X (online in the clinic)	X (online from home)
cognitive tests	X (online in the clinic)	X (online in the clinic)	X (online from home)
blood pressure	X	X	
heart rate variability	X	X	
6-minute walk test	X	X	
discharge letter		X	

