Although increasing importance is being placed on incorporating the patient perspective into research, it was unfortunately not possible to involve a patient advisory board (“lived experience”) due to time and organizational constraints. This would be highly desirable for future projects. Instead, patient feedback was gathered through other channels, such as consultations with experienced clinicians and informal input during the pilot phase. However, we are aware that having a dedicated advisory board would have further improved the development process. In future phases of the project, we plan to incorporate more structured patient feedback to optimize the relevance and acceptability of the intervention. We have trialed the intervention with test subjects and patients, and incorporated their feedback into our manual. Another limitation is that the information from the questionnaires is based on self-reports. The results may be distorted, especially when it comes to pension applications, for example. It would certainly also be informative to evaluate the interviews qualitatively or to review the journals. However, for ethical and methodological reasons, this is not possible in the current study and should be considered for follow-up projects. Another limitation of the study is that, due to organizational differences between clinics and funding, it is not yet possible to determine whether the interventions will be carried out by the same therapists who treat the patients or by therapists unknown to the patients. This potential inconsistency in the therapeutic relationship may affect the therapeutic alliance and the overall treatment experience, which could influence the results. To mitigate this issue, future studies could consider measures to ensure therapist continuity. We attempt to reduce this influence by training all study therapists in a standardized manner in the implementation of the manual.

Despite these limitations, the study provides important information about the far-reaching effects of PCS. For healthcare providers, this means taking patients seriously, creating interdisciplinary treatment options, and taking a differentiated approach to the syndrome. In addition, health policy strategies are needed to adequately address the long-term consequences of the pandemic, including rehabilitation and vocational reintegration. From a scientific perspective, further research on the etiology and therapeutic options is urgently needed.

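### The self-reported primary outcome at T2 is tied to an unspecified psychotherapy session; it should be completed outside therapy, in the same way in all three arms

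*Protocol article*

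**What the plan says.** Section 2.5.7 (Outcomes) of the protocol article names the WAI as primary endpoint and describes it as a measure of subjective work ability. The questionnaires are used in all three groups at T1, T2 and T3. On duration of stay it says: "Rehabilitation usually ends after 3 to 4 weeks". On the T2 occasion it then says: "The final measurements for the study are taken during the last psychotherapy session in the final week". T3 is completed from home six months later, so I read this last sentence as referring to T2.

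The next paragraph of the same section adds: "The assessment sessions are expected to take between 70 and 90 minutes per assessment". It allows breaks, later continuation, paper forms and, where needed, completion in the patient's room.

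Table 2 (section 2.5.8) heads the column "T2 on discharge from rehabilitation" and shows the questionnaires as completed online at the clinic.

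On the people involved, section 2.5.1 states: "All treating providers are aware of the participants’ condition assignments". Section 3.1 leaves one point open and gives funding and the way each clinic is organized as the reasons: "it is not yet possible to determine whether the interventions will be carried out by the same therapists who treat the patients".

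On the intervention contacts, section 2.5.2.2 says of FRAME: "The intervention is carried out as individual therapy in three sessions with one session per week". JOURNAL (section 2.5.2.1) has "two short appointments (sessions) lasting no more than 20 minutes"; a trained research assistant hands out its booklet and completes its documentation form.

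**The concern.** T2 is the time point of both main hypotheses, each of which compares an intervention arm with treatment as usual (TAU) on WAI change from admission to discharge. FRAME is an expectation intervention delivered by a therapist. The sample script in section 2.5.2.2 praises the decision to take part and links belief in a treatment to better results, and in session 3 the patient goes back over earlier expectations with the therapist. If the patient then rates work ability in a session led by that same person, the answer may partly reflect what the therapist is felt to hope for.

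Neither comparison arm has a FRAME therapist. JOURNAL patients work as independently as possible, and TAU patients have no study intervention. A reporting shift present in FRAME and absent in TAU would enter the FRAME-TAU contrast directly and could not be told apart from a true gain. Section 3.1 concedes that self-reports may be distorted, but its example is pension applications, not the setting in which the form is filled in.

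**Working it through.** **1. Which session is meant?** The sentence does not say. There are two readings.

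- *Last routine psychotherapy session, in any arm.* All arms receive psychosomatic rehabilitation, in which psychotherapy is frequently used (section 2.1), and the paragraph speaks of all three groups. This is the more natural reading.
- *Last FRAME session.* With one session per week, session 3 falls in week 3 if session 1 is in week 1. That is the final week of a 3-week stay but not of a 4-week stay. This reading would also leave TAU and JOURNAL without a T2 occasion.

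**2. Does the routine-session reading remove the issue?** Not fully. The provider knows the allocation (section 2.5.1), and section 3.1 leaves open whether the treating therapist also delivers the intervention. Where it is the same person, a FRAME patient completes T2 with the deliverer of the expectation work, while a TAU patient completes it with a therapist who delivered none. Section 3.1 attributes the uncertainty partly to differences between clinics, so the arrangement could hold at one clinic and not at the other.

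**3. Does the assessment fit the sessions described?** Shortfall = assessment time minus session time. The smallest value pairs the shortest assessment with the longest session; the largest pairs the reverse.

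| Contact | Stated length (min) | Smallest shortfall | Largest shortfall |
|---|---|---|---|
| FRAME sessions 2 and 3 (Table 1) | 20 to 30 | 70 − 30 = 40 | 90 − 20 = 70 |
| FRAME session 1 (Table 1) | 50 to 60 | 70 − 60 = 10 | 90 − 50 = 40 |
| Routine psychotherapy session | not given | not computable | not computable |

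These shortfalls assume that the session has no content of its own, yet Table 1 gives each FRAME session a full agenda. The 70 to 90 minutes are not broken down by instrument, so the time for the WAI alone is unknown.

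**4. How large could a reporting shift be?** The document has no figure for this. The following is an illustration on assumed values only: 28 per arm (section 2.5.9), two-sided alpha 0.05 (assumed; the protocol states none), no true effect, and a shift of b standard deviations of WAI change in one arm. For two time points, the group-by-time test equals a t test on change scores, with 28 + 28 − 2 = 54 degrees of freedom and noncentrality b × √(28/2) = 3.74b.

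| Assumed b | Noncentrality | Chance of a significant result |
|---|---|---|
| 0.1 | 0.37 | 6.6% |
| 0.2 | 0.75 | 11.4% |
| 0.3 | 1.12 | 19.7% |
| 0.5 | 1.87 | 45.1% |

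This shows sensitivity to a shift if there is one. It is not evidence that there is one.

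**The case against.** A reader might infer that the plan builds a FRAME-specific bias into the primary endpoint. The text does not support that. It does not name FRAME session 3, the paragraph covers all three groups, and on the natural reading the setting is nominally common to all arms. Nor does it say that a therapist administers, watches or sees the WAI: section 2.7.1 describes digital self-assessment on an online platform, and section 2.7.4 restricts access to the data to authorized study personnel. This stands. An effect that differs between arms is a possibility left open, not something the protocol prescribes.

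A reader might also infer that T2 cannot be carried out as described. That goes too far. The shortfall is shown only for FRAME sessions, routine session length is not given, and questionnaires may be continued later or completed in the room. Those options are accommodations to a stated default, however, and they leave the setting free to vary between patients and arms.

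A conflict with Table 2 is a further tempting reading. It does not hold: a discharge assessment is compatible with the final week, and online completion at the clinic is compatible with a session held there.

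Finally, patients who know they received an expectation intervention may report favourably wherever they sit, and the article already discloses unblinded providers, self-report and the preliminary nature of its results. That is fair. Moving T2 out of therapy removes only the part of the problem that comes from the setting.

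**Conclusion.** The point holds as a cheap improvement to a stated procedure. The protocol ties an unblinded, self-reported primary outcome to a therapy session without saying which session or who is present, in a trial where one arm is a therapist-delivered expectation intervention. A demand effect that differs between arms may follow if the therapist in that session also delivered FRAME, which section 3.1 leaves undetermined, and if the therapist's presence influences answers, which is an inference. Its size cannot be estimated from the document. Separately, the stated assessment time exceeds every FRAME session described, by 10 to 70 minutes across the combinations above. No sample size figure changes.

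**What to change.** Replace the sentence in section 2.5.7 with a rule along these lines:

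- T2 questionnaires are self-completed, online or on paper, outside any therapy or intervention session.
- The pre-discharge window and the setting are the same in all three arms.
- Nobody who treats the patient or delivers FRAME or JOURNAL is present. This includes the research assistant who hands out the JOURNAL booklet, since using that person would recreate an arm-specific setting in JOURNAL.
- Patients are told that these people do not see their answers.

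Word the T2 column of Table 2 to match.

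The cost is a separate T2 time slot, which an assessment of 70 to 90 minutes largely calls for anyway, and someone outside treatment and intervention delivery to organize it. General demand effects from unblinded self-report remain and should stay listed among the limitations.
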